### Statistical analysis

We will compare estimates of patients who receive UF therapy with those who receive conventional pharmacologic therapy. Concomitant medication and other baseline characteristics will be utilized in subgroup analysis.

Continuous variables will be summarized using descriptive statistics. Qualitative variables will be summarized by counts and percentages.

We will compare baseline characteristics. T-test or sign rank test will be used after testing for normality. Chi-square or Fisher’s exact test will be performed for categorical variables.

The primary efficacy endpoint (change of weight loss and dyspnea severity score) will be analyzed by Kaplan-Meier method, and comparisons between two groups will be performed using a log-rank test. Hazard ratio with 95% CI will be derived by the Cox proportional hazards model. Subgroup analyses of the efficacy endpoint are performed for the evaluation of impact of major clinical features on the improvement of primary efficacy endpoints by early UF therapy. Specific information is as follows:
The ability to predict the therapeutic effect of UF by patients’ individual characteristics as well as systolic blood pressure, heart rate, severity of edema, renal and hepatic function, NYHA classification, left ventricular ejection fraction, chamber diameter, concomitant disease and medication;The influence of different patients’ individual characteristics including gender, age, height and weight on the effect of UF for fluid removal and alleviation of dyspnea;The influence of baseline systolic blood pressure and heart rate on the effect of UF for fluid removal and alleviation of dyspnea;The influence of baseline severity of edema (i.e., edema of lower extremity and congestion of other organs) on the effect of UF for fluid removal and alleviation of dyspnea;The influence of baseline renal and hepatic function on the effect of UF for fluid removal and alleviation of dyspnea;The influence of different baseline cardiac function (including NYHA classification and left ventricular ejection fraction) on the effect of UF for fluid removal and alleviation of dyspnea;The influence of different baseline chamber diameter on the effect of UF for fluid removal and alleviation of dyspnea;The influence of different baseline concomitant disease on the effect of UF for fluid removal and alleviation of dyspnea;The influence of different concomitant medication on the effect of UF for fluid removal and alleviation of dyspnea;

Subgroup analysis of primary efficacy endpoint will be estimated using a stratified Cox model. The subgroup analysis will be tested by chi-square or Fisher’s exact tests.

The primary safety endpoints and secondary endpoints will be presented by summary statistics, as number of patients, event counts and percentage, variable counts and percentage.

All comparisons will report *p* values on the basis of 2-sided tests, and a p value ≤ 0.05 will be considered statistically significant. All statistical analyses will be performed using SPSS Statistics version 22 software.

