Currently, UF recommend by most of the guidelines are usually considered for patients with refractory congestion not responding to medical therapy. Previous research found although UF improve hemodynamics in acute decompensated HF refractory to standard medical therapy, it was also associated with high incidence of renal function damage and high in-hospital mortality [6]. However, other research found UF within 12 h of hospitalization in HF patients with volume overload and LD resistance before IV LDs effectively decreased length of stay and readmissions up to 3 months without change of renal function [7]. At present, most of the studies support UF should be considered as early treatment strategies (24 h after admission) in patients with severe HF instead of a “rescue therapy”. Early UF may prevent undesirable cardiorenal syndrome and sodium-volume overload before renal tubular damage induced by further neurohormonal activation and side effects caused by high dose LDs [8, 9].

Taken together, previous related studies showed UF is more effective in decongestion, haemodynamic variables and clinical outcome improvement, as well as restoring LD responsiveness compared with LDs. But most of the studies were based on the foreign population and did not define the exact time period from admission to UF. We do not have the related data for early UF in Chinese population. Furthermore, former study did not define how to screen out the patients recommended for early UF by specific scoring system. Our study aims to determine if early UF 24 h within admission in acute HF is superior to IV LDs in clinical parameter improvement without adverse events and prevents rehospitalization up to 30 days in Chinese population.

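### Two separate wording faults: a paired signed-rank test is named for unmatched arms, and major bleeding and 30-day rehospitalization get only summary statistics although the aims on them are comparative

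*Protocol article*

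**What the plan says.** Everything here is in the protocol article.

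- **Design.** Under Study overview, patients enter the two arms sequentially in a 1:1 ratio, 20 per arm. No matching is described.
- **Test paragraph (Statistical analysis).** It opens "We will compare baseline characteristics", continues "T-test or sign rank test will be used after testing for normality", and closes "Chi-square or Fisher’s exact test will be performed for categorical variables". No other non-parametric test for continuous data is named.
- **General intention.** The section begins "We will compare estimates of patients who receive UF therapy with those who receive conventional pharmacologic therapy", without naming a method, and later says that all comparisons will carry two-sided p values.
- **Primary efficacy.** This has its own method: "comparisons between two groups will be performed using a log-rank test", with a Cox hazard ratio and 95% interval.
- **Safety and secondary endpoints.** "The primary safety endpoints and secondary endpoints will be presented by summary statistics, as number of patients, event counts and percentage, variable counts and percentage".
- **Aim.** The Background says the study will determine whether early ultrafiltration "is superior to IV LDs in clinical parameter improvement without adverse events and prevents rehospitalization up to 30 days in Chinese population". The Discussion paragraph of the Abstract repeats this.
- **Status of the endpoints.** Under Study outcomes, major bleeding by TIMI or GUSTO criteria is a primary endpoint. Heart failure rehospitalization and death within 30 days of discharge are secondary.

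**The concern.** There are two points, and neither depends on the other.

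**The test name.** A signed-rank test works on within-pair differences or on a single sample. Between two unmatched arms there are no pairs, so someone must create them, most likely by row order in the data file. The same 40 values sorted differently then give a different p value. If the arms end up unequal, through dropout or a missing value, the test cannot be run at all.

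**Aim against analysis.** The plan sets out to draw comparative conclusions on adverse events and readmission, but tabulates those endpoints without a difference or an interval. This is a stated method, not silence, and it contrasts with the hazard ratio and interval given to primary efficacy. The risk lies in interpretation: a table showing no major bleeds would be read as safety, and a raw difference in readmissions as prevention. In addition, counts and percentages do not suit continuous secondary endpoints such as net fluid loss, NT-proBNP or creatinine.

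**Working it through.** The article gives no power, effect size, standard deviation or event rate, so there is no figure of its own to reproduce. Inputs from the article: 20 per arm, two-sided 5% level, unmatched arms. Everything marked as assumed is not in the article.

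**1. Signed-rank test on independent arms (simulation, assumed distributions).**

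- *One fixed data set.* 20 lognormal values per arm, the second arm multiplied by exp(0.6). Re-pairing the arms at random 5,000 times gave signed-rank p values from 0.00004 to 0.097, with a median of 0.009. The rank-sum p was 0.015 and does not depend on order.
- *Unequal arms.* With 20 against 18 values the signed-rank test could not be run.
- *Long-run behaviour over 20,000 simulated trials, arms paired by list order:*

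| Data | Effect | Signed-rank: share p ≤ 0.05 | Rank-sum: share p ≤ 0.05 |
|---|---|---|---|
| Normal | none | 0.050 | 0.052 |
| Normal | shift 0.9 | 0.75 | 0.77 |
| Lognormal | none | 0.049 | 0.050 |
| Lognormal | 0.9 on log scale | 0.70 | 0.77 |

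The test is not anti-conservative on average. The faults are an arbitrary p value in any one trial, some lost power, and failure with unequal arms.

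**2. Which variables the sentence governs.** Read with the sentence before it, it covers baseline characteristics. Read as covering all variables, it also covers non-normal continuous outcomes. On that second reading, chi-square or Fisher applies to bleeding, death and readmission, which are binary. On neither reading does the signed-rank wording touch the binary endpoints.

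**3. What a count of zero can show.** The exact two-sided 95% upper limit for 0 events in n patients is 1 − 0.025^(1/n). With n = 20 this is 1 − 0.025^(1/20) = 1 − 0.8316 = 0.168, or 16.8%.

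For the difference between arms, take 0/20 against 0/20. The Wilson upper limit for one arm is z²/(n + z²) = 3.84/(20 + 3.84) = 0.161. The hybrid score interval for the risk difference is then ±√(0² + 0.161²), or −16.1 to +16.1 percentage points. A table with no bleeds in either arm would therefore still allow a difference of about 16 points in either direction.

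**4. How far apart the counts must be.** For 0 against k events of 20, the two-sided Fisher p is 2·C(20,k)/C(40,k).

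- k = 4: 2 × 4,845/91,390 = 0.106
- k = 5: 2 × 15,504/658,008 = 0.047

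**5. Readmission, with assumed 30-day rates.** Exact Fisher power at 20 per arm: 20% v 10%, 7%; 30% v 10%, 24%; 40% v 10%, 49%; 50% v 10%, 74%. These figures describe the sample size. Naming a test would not change them. They bear only on how the aim should be worded.

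**The case against.** A reader might infer that the trial has no valid between-group comparison at all, and that the signed-rank wording is what leaves the safety and readmission claims unsupported. The article does not bear this out:

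- The sentence follows one on baseline characteristics, so on its natural reading it governs no endpoint.
- The next sentence names valid two-sample tests for categorical data.
- The t-test is valid for normal data, and primary efficacy has a between-group log-rank test (whether that suits weight and dyspnea change is a separate matter).
- The section states a general intention to compare the arms.

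All of this stands. The gap on bleeding and readmission rests on the summary-statistics sentence alone.

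Three further objections carry weight. The test name, set beside a t-test, is plausibly a slip for rank-sum; that makes the fix easy, but the text is still wrong as written. The section elsewhere gives continuous variables descriptive statistics, so it would be too strong to say that NT-proBNP or creatinine will be shown only as counts; the later sentence is loosely worded. Finally, descriptive reporting of safety and secondary endpoints is defensible at 20 per arm, and a full protocol or analysis plan, not shown, may name methods. What remains is that a descriptive analysis cannot be combined with an aim to determine superiority without adverse events and prevention of readmission. One of the two has to change.

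**Conclusion.** Both points hold in limited form.

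**(1)** The signed-rank test is the wrong procedure for two unmatched arms. The fault certainly affects the baseline comparisons and may affect non-normal continuous outcomes. It is minor: average type I error is near 0.05, and power falls from 0.77 to 0.75 (normal) or 0.70 (lognormal) in the simulated settings. However, the p value in a single data set is arbitrary. The p range quoted comes from one simulated data set and illustrates the problem; it does not predict its size in this trial.

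**(2)** The analysis stated for major bleeding and 30-day rehospitalization does not match the comparative aims. This is the more important point. The 16.8% limit and the Fisher thresholds need only the planned 20 per arm. The power figures rest on assumed rates and are background.

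**What to change.** 1. Replace the signed-rank test with the Wilcoxon rank-sum (Mann-Whitney) test, and say whether that paragraph covers baseline variables only or outcomes as well.
2. In the sentence on safety and secondary endpoints, add that major bleeding, death and rehospitalization will be reported as between-group risk differences with an exact or score 95% interval, and continuous secondary endpoints as between-group differences with 95% intervals. Limit counts and percentages to categorical endpoints.
3. In the Abstract and Background, reword the aim so that the trial estimates the effects on adverse events and 30-day rehospitalization, instead of determining their absence or prevention.

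These are changes of wording. They use data the trial already plans to collect and leave visits, treatment and sample size untouched. The price is a more modest stated aim, and intervals that will be visibly wide at 20 per arm.

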**Fig. 1 Fig1:**
[figure not shown]
Study design. The control group will be treated with intravenous loop diuretics by experienced HF cardiologists according to guideline recommendations. Patients of the early UF group will receive a single or repeated session of UF started within 24 h from admission until the relief of patient’s symptom. HF, heart failure; UF, ultrafiltration

The trial aims to recruit 40 patients (20 patients for each group) over an estimated 24-month period. After baseline visit, follow-up visit will occur at the end of study treatment, 24 h, 48 h, and 72 h after the end of study treatment, at discharge, and 30 days after discharge. At the baseline visit, informed consent will be taken, and additional baseline variables including gender, age, height, weight, occupation, race, physical activity, complete medical history (including history of smoking and drinking, past and present medical history, concomitant disease), vital signs, NYHA classification, dyspnea severity score, score by Minnesota Living with Heart Failure Questionnaire (MLWHFQ) functional capacity, physical examination including distention of jugular vein, edema of lower extremity and congestion of other organs, laboratory test, electrocardiogram, chest X-ray, echocardiographic data and concomitant drug used up to 3 months before enrollment will be recorded.

Questionnaires (dyspnea severity score and score by MLWHFQ functional capacity) at follow-up visits will also be collected by trained clinicians. This will aid in our assessment of patients’ cardiac function and other safety data.

During follow-up, we will record all the primary and secondary end points and adverse events. All adverse events will be evaluated according to severity, causality, expectedness, and relationship to study treatment. Subjects who develop complications that, in the judgment of principal investigator or sub-investigator, are not suitable to continue the trial will be screened out from the study. Participants will continue with follow-up and may restart study protocol if the clinical situation resolves. Investigators are responsible for the decision to resume the study. If treatment according to the study protocol is clinically insufficient, the study will be suspended and effective treatment should be applied according to the current clinical practice.

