### Study outcomes

The primary end points of EUC-CHF are the changes of weight loss and dyspnea severity score at every scheduled visit which are considered as the part of a single composite endpoint, as well as the occurrence of clinically major bleeding defined by TIMI or GUSTO criteria [12].

Secondary outcomes include: net fluid loss, length of stay in CCU or ICU, change of score by MLWHFQ functional capacity, change of serum and ultrafiltrate concentrations of endotoxin, ET-1, TNF-a, IL-6 and IL-10, changes of cardiac function (the NYHA classification), changes in N-terminal proB-type natriuretic peptide (NT-proBNP) level, changes of LDs dose, HF rehospitalizations for congestive HF in 30 days after discharge, cardiovascular death and all-cause death in 30 days after discharge, change of blood pressure, changes in hepatic and renal function (serum creatinine concentration, estimated glomerular filtration rate [eGFR]), serum electrolytes, hemoglobin and incidence of acute coronary syndrome at scheduled visits.

Weights will be obtained at every scheduled visit using the same balance with the patient shoeless in a hospital gown after emptying the bladder. Weight loss is the difference between weight at baseline and the weight recorded at subsequent visits.

The dyspnea severity score by a proposal to standardize dyspnea measurement in clinical trials of acute heart failure syndromes by International Working Group on acute heart failure of European Society of Cardiology is used for the assessment of dyspnea [13].

Total fluid intake and output (ultrafiltrate and urine) measured at every scheduled visit after enrollment will be used to calculate net fluid losses.

Glomerular filtration rate will be calculated according to the abbreviated Modification of Diet in Renal Disease (MDRD) equation [14].

Acute coronary syndrome includes unstable angina, ST segment elevated myocardial infarction and non-ST segment elevated myocardial infarction. Myocardial infarction is defined according to the fourth universal definition of myocardial infarction [15]. Death will be considered cardiac according to the 2014 ACC/AHA key data elements and definitions for cardiovascular endpoint events in clinical trials [16].

We also will collect all the urine output after patients are enrolled to receive standard medical therapy or early UF until 72 h after the end of study treatment. Then we will measure the average urine electrolytes for every enrolled patient.

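### The primary efficacy endpoint is a repeated change in weight and dyspnea score, yet it is assigned Kaplan-Meier, log-rank and Cox methods with no event stated, so the hazard ratio is undefined as written

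*Protocol article*

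**What the plan says.** The endpoint is set out in the Protocol article under Study outcomes. The efficacy part of the primary endpoint is the "changes of weight loss and dyspnea severity score at every scheduled visit which are considered as the part of a single composite endpoint". For the weight component, "Weight loss is the difference between weight at baseline and the weight recorded at subsequent visits". The dyspnea component is a published severity score, which "is used for the assessment of dyspnea"; no value or change on it is named as improvement or worsening.

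The method is set out under Statistical analysis. It opens with the estimator: "The primary efficacy endpoint (change of weight loss and dyspnea severity score) will be analyzed by Kaplan-Meier method". The test is the log-rank test. The effect measure follows: "Hazard ratio with 95% CI will be derived by the Cox proportional hazards model". For subgroups, "Subgroup analysis of primary efficacy endpoint will be estimated using a stratified Cox model".

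The visit schedule, in the text after Fig. 1, is that "follow-up visit will occur at the end of study treatment, 24 h, 48 h, and 72 h after the end of study treatment, at discharge". A last visit follows 30 days later. The planned size is 20 patients per group, and tests are two-sided at 0.05.

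**The concern.** Kaplan-Meier curves, the log-rank test and the Cox model describe the time from a defined origin to a defined event, with a rule for patients who do not reach it. The stated endpoint is a difference in kilograms and a score, each measured several times per patient. The article supplies nothing that turns these into a time to event.

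This is the only efficacy comparison for which the article names a primary test and effect measure. As written, it cannot be run until someone supplies an event that the article does not contain. The resulting hazard ratio would describe that event. It would not estimate how many more kilograms were lost, or how much dyspnea improved, which is what the endpoint describes. In a trial of 40 patients, reducing a measured quantity to yes or no also gives up power that the trial can ill afford.

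**Working it through.** **1. Endpoint and method side by side.** The article gives no power, effect size, SD or event rate for its 40 patients, so there is no figure to reproduce. The main check is what a survival analysis needs against what the article states.

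- Event: no kilogram threshold, no dyspnea cut-off and no rule for combining the two into one event.
- Direction: not stated whether the event is improvement or worsening.
- Time origin: not stated. Visits are counted from the end of study treatment. In the ultrafiltration group treatment runs until symptoms are relieved (Study overview), so its length can differ between patients and between arms.
- Censoring: no rule.
- Event times: values are seen only at a few visits, so any event time is known only to lie between visits and many will be tied.

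The outcomes that are events (major bleeding, death, heart-failure rehospitalization, acute coronary syndrome) are safety or secondary outcomes, which Statistical analysis limits to summary statistics.

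**2. Dependence on the cut-off, one visit.** Assumed, because the article gives no values: mean loss 5 kg with ultrafiltration and 3 kg in control, SD 3 kg, normal. The proportion losing at least c is Φ((mean − c)/SD).

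- Any loss (c = 0): Φ(5/3) = 95% and Φ(3/3) = 84%, a gap of 11 points.
- At least 4 kg: Φ(1/3) = 63% and Φ(−1/3) = 37%, a gap of 26 points.

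**3. Dependence on the cut-off, several visits.** Assumed mean losses at end of treatment, +24, +48 and +72 h: 2.0, 2.6, 3.2 and 3.6 kg in control; 4.0, 4.1, 4.1 and 4.1 kg with ultrafiltration. Between-patient SD is 2.0 kg and within-patient SD 0.8 kg. The event is the first visit with a loss of at least X kg. One large simulated data set, Cox model with Breslow ties, gives:

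| X (kg) | Hazard ratio | Events tied at first visit |
|---|---|---|
| 1 | 1.31 | 84% |
| 2 | 1.45 | 75% |
| 3 | 1.60 | 67% |
| 4 | 1.73 | 58% |
| 5 | 1.87 | 51% |
| 6 | 2.04 | 45% |

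The data are the same in every row; only the unstated event changes.

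**4. Power given up.** Inputs: 20 per arm and two-sided 0.05 from the article; standardized differences d assumed.

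- Comparison of means: noncentral t with 38 degrees of freedom and noncentrality d√(20/2) = d√10. Power is 69% at d = 0.8 and 87% at d = 1.0.
- Midpoint split at one visit: event proportions Φ(d/2) and 1 − Φ(d/2), that is 65.5% and 34.5% at d = 0.8, and 69.1% and 30.9% at d = 1.0. With a single visit the log-rank statistic is (a − m/2)²/V, where a is the number of events in one arm, m the total number of events, and V = 20·20·m(40 − m)/(40²·39). Summing the binomial probabilities of all tables where it reaches 3.84 gives power of 48% and 67%.

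The loss is about 21 points at 0.8 SD (69 − 48) and 20 points at 1.0 SD (87 − 67).

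**The case against.** The best reply is that time to improvement is a legitimate endpoint and may be what was meant. The article refers to improvement of the primary efficacy endpoints and to blinded adjudication of endpoint events. An event definition and censoring rule could sit in a full protocol or SAP that is not shown. This stands in part: a reader might infer that the hazard ratio has no possible meaning, and that goes too far. It does not remove the mismatch, because the article fixes both the endpoint and the method. A SAP that defined a responder event would change the endpoint given under Study outcomes, and one that analysed change scores would change the method given under Statistical analysis.

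Three other inferences are tempting and not supported.

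- *The cut-off will be picked after seeing the data.* Nothing says so. An unseen SAP could fix it in advance, and the adjudicator and the statistician are described as blinded to allocation. What can be said is that the article states no cut-off.
- *The analysis ignores baseline.* Weight loss is itself a difference from baseline. What is absent is adjustment for the baseline value as a covariate.
- *Baseline adjustment would bring a large gain in precision for weight.* With equal variances, ANCOVA has (1 + ρ)/2 of the variance of a change score, and SD of change = SD of weight × √(2(1 − ρ)). If the SD of change is 3 kg and the SD of body weight is an assumed 10 to 15 kg, then ρ = 1 − 9/(2·10²) = 0.955 to 1 − 9/(2·15²) = 0.98. The reduction is only about 1% to 2%.

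The power figures in step 4 are also only an illustration. They concern one visit and one split, whereas the stated log-rank test would run over several visits.

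**Conclusion.** The concern holds as a mismatch between two stated parts of the plan. The primary efficacy endpoint is a repeated change in two measurements, and the primary test, the effect measure and the subgroup model all require an event that the article does not state. As written the hazard ratio is undefined. Once some event is supplied, its value depends on that choice, and it does not estimate the difference in weight or dyspnea. This part rests on the text alone and needs no assumption.

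The sizes rest on assumed values. They show that the choice of cut-off matters and that roughly 20 points of power can be lost at differences of 0.8 to 1.0 SD. They are not predictions for this trial. Because the defect lies in the primary analysis, it must be corrected before the data are analysed.

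**What to change.** Replace the survival methods for the primary efficacy endpoint, including the stratified Cox subgroup model, with an analysis of change from baseline:

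- Name one primary visit.
- Weight: ANCOVA, or a mixed model for repeated measures, adjusted for baseline weight; report the difference in kg with its 95% CI.
- Dyspnea score: ANCOVA or a proportional-odds model, adjusted for the baseline score.
- State how the two components yield one primary conclusion, for example that both must be significant, or that either may succeed under a multiplicity adjustment.
- Examine subgroups within the same models.

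No new data are needed, since weight and dyspnea score are already recorded at baseline and follow-up. It is more than a change of analysis wording, however: the single-composite wording under Study outcomes must be revised, and a both-must-succeed or adjusted rule is somewhat stricter than one test.

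If time to improvement is what is intended, the alternative is to rewrite Study outcomes before analysis so that it defines the event, the time origin and the censoring rule, and to use methods that allow for tied, visit-based event times.
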